## Abstract

**Background:**

Advances in hematopoietic cell transplantation (HCT) have led to marked improvements in survival. However, adolescents and young adults (AYAs) who undergo HCT are at high risk of developing sarcopenia (loss of skeletal muscle mass) due to the impact of HCT-related exposures on the developing musculoskeletal system. HCT survivors who have sarcopenia also have excess lifetime risk of non-relapse mortality. Therefore, interventions that increase skeletal muscle mass, metabolism, strength, and function are needed to improve health in AYA HCT survivors. Skeletal muscle is highly reliant on mitochondrial energy production, as reflected by oxidative phosphorylation (OXPHOS) capacity. Exercise is one approach to target skeletal muscle mitochondrial OXPHOS, and in turn improve muscle function and strength. Another approach is to use “exercise enhancers”, such as nicotinamide riboside (NR), a safe and well-tolerated precursor of nicotinamide adenine dinucleotide (NAD^+^), a cofactor that in turn impacts muscle energy production. Interventions combining exercise with exercise enhancers like NR hold promise, but have not yet been rigorously tested in AYA HCT survivors.

**Methods/design:**

We will perform a randomized controlled trial testing 16 weeks of in-home aerobic and resistance exercise and NR in AYA HCT survivors, with a primary outcome of muscle strength via dynamometry and a key secondary outcome of cardiovascular fitness via cardiopulmonary exercise testing. We will also test the effects of these interventions on i) muscle mass via dual energy x-ray absorptiometry; ii) muscle mitochondrial OXPHOS via an innovative non-invasive MRI-based technique, and iii) circulating correlates of NAD^+^ metabolism via metabolomics. Eighty AYAs (ages 15-30y) will be recruited 6–24 months post-HCT and randomized to 1 of 4 arms: exercise + NR, exercise alone, NR alone, or control. Outcomes will be collected at baseline and after the 16-week intervention.

**Discussion:**

We expect that exercise with NR will produce larger changes than exercise alone in key outcomes, and that changes will be mediated by increases in muscle OXPHOS. We will apply the insights gained from this trial to develop individualized, evidence-supported precision initiatives that will reduce chronic disease burden in high-risk cancer survivors.

**Trial registration:**

ClinicalTrials.gov, NCT05194397. Registered January 18, 2022, https://clinicaltrials.gov/ct2/show/NCT05194397 {2a}.

**Supplementary Information:**

The online version contains supplementary material available at 10.1186/s12885-022-09845-1.

## Background

Advances in hematopoietic cell transplantation (HCT) have led to 10% improvements in survival each decade since the 1980s [1]. Research in the growing population of long-term HCT survivors has highlighted the chronic and debilitating co-morbidities associated with toxicity from pre-HCT exposures, HCT conditioning, immunosuppression, and graft versus host disease (GvHD) [2]. Adolescents and young adults (AYAs) who undergo HCT are at an especially high risk of developing sarcopenia (loss of skeletal muscle mass), a consequence of HCT-related exposures on the developing musculoskeletal system [3]. HCT-associated risk factors for sarcopenia include inflammation related to GvHD, treatment-related myopathy (e.g., from glucocorticoids), undernutrition, physical inactivity, and/or de novo co-morbidities (e.g., hypogonadism, growth hormone deficiency) that develop during or shortly after HCT [4]. In AYAs undergoing HCT, we have shown that sarcopenia occurs earlier than would be expected from advancing age alone, likely because the AYA age range (15-30y) represents a critical window for attainment of peak muscle mass. We have also shown that HCT survivors who have sarcopenia have twice the risk of non-relapse mortality as compared to survivors without sarcopenia, which may be mediated in part by an excess incidence of premature cardiovascular disease (CVD) [5]. Therefore, evidence-based interventions are needed that will increase skeletal muscle mass, metabolism, strength, and function and ultimately improve health outcomes in AYA HCT survivors (Table 1).

**Table 1 Tab1:** World Health Organization Trial Registration Data Set {2b}

**Data category**	**Information** {2b}
Primary registry and trial identifying number	ClinicalTrials.gov NCT05194397
Date of registration in primary registry	January 18, 2022
Secondary identifying numbers	20–017,320 1R01CA254955-01A1 (U.S. NIH Grant/Contract)
Source(s) of monetary or material support	National Cancer Institute (NCI)
Primary sponsor {5b}	National Cancer Institute Sponsor’s Reference: 1R01CA254955-01A1 Contact name: [name] Address: [name] Telephone: [name] Email: [contact]
Secondary sponsor(s)	
Contact for public queries	[name], MSCE [name] [contact]
Contact for scientific queries	[name], MSCE [name] [contact]
Public title	Exercise Training and NR Supplementation Trial to Improve Fitness in AYA HCT Survivors
Scientific title	Intensive Tailored Exercise Training With NAD + Precursor Supplementation to Improve Muscle Mass and Fitness in Childhood Cancer Survivors
Countries of recruitment	United States of America
Health condition(s) or problem(s) studied	Acute Lymphoblastic Leukemia in Remission, Cancer Survivors
Intervention(s)	Dietary Supplement: Nicotinamide Riboside—GMP-grade 300 mg capsules of the dietary supplement nicotinamide riboside (ChromaDex, Irvine CA) Placebo—same excipients without the active supplement and is generally recognized as safe Other: Exercise Intervention—at-home training sessions and will include aerobic and strengthening components designed to progress persons gradually to 150–300 min of the equivalent of moderate aerobic activity, and twice weekly strengthening over 16 weeks
Key inclusion and exclusion criteria	Ages eligible for study: 15 – 30 years at enrollment, inclusive Sexes eligible for study: both Accepts healthy volunteers: no Inclusion Criteria: Males and females, ages 15–30 years at enrollment; able to understand and speak English; diagnosis of acute leukemia (myeloid, lymphoid) requiring allogeneic HCT; 6–24 months from allogeneic HCT; if female, negative urine/serum pregnancy test and must use an acceptable method of contraception, including abstinence, a barrier method (diaphragm or condom), Depo-Provera, or an oral contraceptive, for the duration of the study; Parental/guardian permission (informed consent) and if appropriate, child assent Exclusion Criteria: Known sensitivity to NR; Concurrent use of any medications, including statins, likely to increase risk of NR toxicity; Active malignancy, investigational agent(s) within 4 wks, or systemic glucocorticoids within 12 wks; Currently meeting public health exercise guidelines; Use of NAD + precursors (supra-physiologic) within 4 weeks; Hemoglobin < 10 g/dL; Platelets < 50 K; Diabetes Mellitus requiring insulin or insulin secretagogue; HbA1C ≥ 8%; Kidney disease (eGFR < 60 ml/min/1.73 m2); Liver disease Alanine aminotransferase/Aspartate aminotransferase(ALT/AST) > 3 × ULN; Limitations in physical function preventing exercise testing/training; Contraindications to MRI; Unstable angina or history of acute myocardial infarction (< 5 days of planned study procedures); Recurrent syncope; Symptomatic severe aortic stenosis; Uncontrolled arrhythmia causing symptoms; Pulmonary embolus < 3 months of study procedures; Thrombosis of lower extremities; Symptomatic moderate or severe persistent asthma based on forced expiratory volume (FEV) from pre-HCT pulmonary function testing; Room air desaturation at rest ≤ 85%; Females: Pregnant or planning pregnancy; Non-cardiopulmonary disorders that may affect exercise performance or be aggravated by exercise (e.g. infection, renal failure, thyrotoxicosis, > moderate graft versus host disease (GVHD) resulting in physical or functional impairment); Parents/guardians or subjects who, in the opinion of the Investigator, may be non-compliant with study schedules or procedures
Study type	allocation: Randomized Intervention Model: Factorial Assignment Intervention Model Description: Randomized, placebo-controlled trial with a 2 × 2 factorial design testing the effects of an NAD + precursor (NR) and exercise Masking: Quadruple (Participant, Care Provider, Investigator, Outcomes Assessor) Masking Description: The participants and the investigator team will be blinded as to the group assignment: NR vs Placebo. All collected data (e.g., questionnaires) will be coded, so initial analysis will be conducted without knowledge of the participant's group status While the assignment of participants to the exercise groups will not be blinded to the participant or majority of the study team, a designated blinded technician will perform the follow-up Cardio Pulmonary Exercise Testing. Follow-Up Cardio Pulmonary Exercise Testing will be performed by a dedicated blinded study team member, an exercise technician, who will not know if the participant was assigned to an arm including the exercise intervention Phase II
Date of first enrolment	June 2022
Target sample size	80
Recruitment status	Recruiting
Primary outcome(s)	Within participant changes in muscle strength (Isometric knee extension, Z-score) [ Time Frame: Baseline to 16 Weeks]
Key secondary outcomes	Within participant change in muscle strength (Ankle Plantarflexion) using Biodex dynamometer [ Time Frame: Baseline to 16 Weeks] Within participant change in grip strength (Hand Grip Dynamometry) [ Time Frame: Baseline to 16 Weeks] Within participant changes in muscle mass (lower leg lean muscle mass by DXA) [ Time Frame: Baseline to 16 Weeks] Within participant changes in post-exercise oxidative phosphorylation capacity (OXPHOS) using non-invasive MRI scanning using creatine chemical exchange saturation transfer (CrCEST) [ Time Frame: Baseline to 16 Weeks] Within participant change in aerobic capacity (VO2 max, Maximal Oxygen Uptake on Cardiopulmonary Exercise Testing). [ Time Frame: Baseline to 16 Weeks]

### Strategies to improve skeletal muscle health

Skeletal muscle is highly reliant on mitochondrial energy production, as reflected by oxidative phosphorylation (OXPHOS) capacity. Thus, one strategy to improve skeletal muscle function is to increase muscle OXPHOS. Exercise (aerobic and resistance training) is a well-established approach to target skeletal muscle mitochondrial OXPHOS, as well as mass, strength, and function, though responsiveness to exercise training interventions may vary in both individuals who are healthy and those who have chronic disease. Moreover, individuals who survive HCT often do not meet minimum public health recommendations for exercise, and also demonstrate significant declines in daily physical activity from pre- to post-HCT [6]. In addition, individuals who develop GvHD are even more likely to be inactive because the disproportionate atrophy that develops in lower extremity and back extensor muscles makes activity more challenging to pursue. The combination of inactivity plus decreased muscle mass further compromises muscle capillary transport and utilization of oxygen, leading to additional impairments in cardiovascular reserve [7]. Thus, targeting physical inactivity along with treatment-related muscle metabolic deficits may produce benefits that are more than additive in sedentary HCT survivors.

Another approach to improve skeletal muscle health is to use an “exercise enhancer” such as precursors of nicotinamide adenine dinucleotide (NAD^+^), a cofactor with myriad roles in cellular metabolism, to recapitulate and/or add to the physiologic benefits of exercise [8, 9]. Nicotinamide riboside (NR) is an NAD^+^ precursor that is consumed as part of the diet and can be administered orally in humans [8]. In preclinical models, NR has been shown to increase muscle OXPHOS capacity and may improve exercise performance [10]. NAD^+^ precursor supplementation with NR has also been shown to increase oxidative metabolism in both muscle [11, 12] and liver [13], and its therapeutic potential is being explored in the wide range of conditions where disordered mitochondrial metabolism occurs, including aging and CVD [14].

Although NR is a niacin analog, unlike niacin, NR is unlikely to produce flushing because it does not activate the niacin receptor (GPR109A) [15]. The pharmacokinetics and pharmacodynamics of NR have been measured in humans [16–18], and safety and toxicity studies in both animals and humans indicate a favorable safety profile that is similar to or better than niacin [18]. Two recent studies in humans found that NR, which is metabolized to nicotinamide, was well tolerated without serious adverse events [19, 20]. Pediatric participants (*n* = 163) who received 1.2 g/m^2^/day of nicotinamide for 5 years had a similar number of serious adverse events as participants receiving placebo (*n* = 166) [21]. A safety study of higher dose (up to 8 g daily) of nicotinamide for up to 8 weeks in individuals with complex neuromuscular disease found it to be generally well-tolerated, with nausea being the predominant side effect observed at the highest doses that resolved spontaneously after dose reduction and/or with anti-nausea treatment [22]. In 12 older men receiving 1 g daily of NR for 21 days, NR was well tolerated, and produced an increase in skeletal muscle NAD^+^ and a decrease in circulating inflammatory cytokines [23]. A longer 12-week trial tested 1,000 mg po twice daily (that is, a total daily dose of 2,000 mg NR) in *N* = 40 healthy sedentary men, and found NR to be well-tolerated over this duration with sustained increases in urinary NAD^+^ metabolites [19] {6b}.

### Rationale for combining exercise with NR to improve muscle health in AYA HCT survivors

Exercise and NAD^+^ precursor supplementation via NR are each independently expected to improve muscle mass and strength in HCT survivors. When combined, exercise and NR may even produce benefits that are synergistic (Fig. 1). Exercise requires energy, and NAD^+^ availability promotes mitochondrial ATP production. Indeed, one of the known physiologic adaptations to exercise training in humans is up-regulation of NAD^+^ salvage via increased expression of NAMPT [24]. Studies in preclinical models demonstrate the relevance of this response. For example, mice who have increased NAD^+^ availability gain more exercise capacity in response to exercise training than their counterparts with typical NAD^+^ availability [25]. Also, increased NAD^+^ availability leads to more sirtuin-dependent PGC-1α related mitochondrial biogenesis with training [25]. Recently released physical activity guidelines emphasize the universal benefits of exercise, including for individuals with health problems [26]. However, exercise can require a disproportionate investment of time and effort for those with chronic conditions. Strategies such as NAD^+^ precursor supplementation that enhance the benefits of training would increase the yield of this important investment and could be a valuable addition to our therapeutic arsenal. Therefore, exercise combined with NAD^+^ precursor supplementation may yield additional benefits compared to either alone, but this approach has not been tested in AYA HCT survivors {6a}.

**Fig. 1 Fig1:**
[figure not shown]
An improvement of overall skeletal muscle health via combination intervention of exercise and NAD + precursor supplementation. Cancer has both direct and indirect effects that compromise cardiovascular reserve capacity, and thus contribute to premature mortality. Both exercise and NAD + precursor therapy (nicotinamide riboside, NR) may increase skeletal muscle mass, mitochondrial OXPHOS capacity, strength, and aerobic capacity. This, in turn, will lead to a lower rate of premature mortality caused by a significant decline in cardiovascular reserve capacity. The figure was generated using Adobe Illustrator (version 22.0)

## Methods/design

In this randomized controlled trial, we will prospectively enroll 80 participants status-post HCT at two sites, the Children’s Hospital of Philadelphia (CHOP) (Philadelphia, PA, USA) and the City of Hope Medical Center (COH) (Duarte, CA, USA). There will be 4 arms: exercise intervention with NR supplementation, exercise intervention with placebo, no exercise intervention with NR supplementation, and no exercise intervention with placebo. The individualized exercise intervention will occur in the home, overseen remotely via Telehealth by exercise intervention physiologists from St. Jude Children’s Research Hospital (Memphis, TN, USA) {9}. Participants who are randomized to the exercise intervention will be given the necessary equipment to participate either before they depart the site or by mail. Each participant will take part in the study for 16 weeks, with a total of three onsite in-person visits: one at baseline, one interim visit at week 8, and a final visit at the end of the 16-week intervention.

The primary objective of this study is to measure the effect of combination administration (NR + exercise) on skeletal muscle quality (strength along with mitochondrial OXPHOS capacity) in AYA HCT survivors {7}. Skeletal muscle quality will be measured by dynamometry, while OXPHOS capacity will be assessed through creatine chemical exchange saturation magnetic resonance imaging (CrCEST MRI). The secondary objective of this study is to measure the effect of combination administration (NR + exercise) on aerobic capacity (VO_2_max), as determined by cardiopulmonary exercise testing (CPET).

### Participants and randomization

Potentially eligible participants will be identified and recruited both at CHOP and COH through existing databases and physician referrals. Study staff will pre-screen potential participants by reviewing the medical charts and exclude those who do not meet inclusion/exclusion criteria {15}. Individuals who meet the eligibility criteria (Table 2) will be invited to enroll. All participants will be enrolled when they provide written consent to the principal investigator(s) either virtually or in-person and all the initial eligibility requirements are met {26a}. Once eligibility is confirmed via in-person screening procedures, participants will be randomized into one of four arms, with randomization stratified by age (≥ 18y or < 18y) and site (CHOP or COH) by a designated study member using REDCAP randomization scheme (Fig. 2) {16b} {16c}. Balance between arms will be maintained through randomly permuted blocks of size four or eight {16a}. The research team, outcomes assessors, care providers, and participants will be blinded with respect to whether participants are receiving NR vs. placebo. NR and placebo are dispensed in identical capsules to avoid un-blinding. The outcomes assessor (but not the study team, care providers, or participants) will be blinded with respect to whether individuals are receiving the in-home exercise intervention vs. no exercise intervention {17a}. The Investigator will be unblinded only if an AE occurs that is determined to be serious, and treatment for the adverse event (AE) depends on knowing the group assignment. Participants/families will be unblinded at the completion of the entire study {17b}. The current study has been approved by the Institutional Review Board of Children’s Hospital of Philadelphia (approval number: IRB #17,320) and has been pre-registered at www.clinicaltrials.gov (NCT05194397). The Standard Protocol Items: Recommendations for Interventional Trials (SPIRIT) guideline was used to generate the report [27].

**Table 2 Tab2:** Inclusion and Exclusion Criteria {10}

Inclusion Criteria	Exclusion Criteria
1. Males and females, ages 15–30 years at enrollment 2. Able to understand and speak English (in order to appropriately follow the intervention) 3. Diagnosis of acute leukemia (myeloid, lymphoid) requiring allogeneic HCT 4. 6–24 months from allogeneic HCT 5. Females must have a negative urine/serum pregnancy test and must use an acceptable method of contraception, including abstinence, a barrier method (diaphragm or condom), Depo-Provera, or an oral contraceptive, for the duration of the study 6. Parental/guardian permission (informed consent) and if appropriate, child assent	1. Known sensitivity to NR 2. Concurrent use of any medications, including statins, likely to increase risk of NR toxicity {11d} 3. Active malignancy, investigational agent(s) within 4 wks, or systemic glucocorticoids within 12 wks 4. Currently meeting public health exercise guidelines 5. Use of NAD^+^ precursors (supra-physiologic) within 4 weeks 6. Hemoglobin < 10 g/dL 7. Platelets < 50 K 8. Diabetes Mellitus requiring insulin or insulin secretagogue 9. HbA1C ≥ 8% 10. Kidney disease (eGFR < 60 ml/min/1.73 m2) 11. Liver disease (ALT/AST > 3 × ULN) 12. Limitations in physical function preventing exercise testing/training 13. Contraindications to MRI 14. Unstable angina or history of acute myocardial infarction (< 5 days of planned study procedures) 15. Recurrent syncope 16. Symptomatic severe aortic stenosis 17. Uncontrolled arrhythmia causing symptoms 18. Pulmonary embolus < 3 months of study procedures 19. Thrombosis of lower extremities 20. Symptomatic moderate or severe persistent asthma based on FEV from pre-HCT pulmonary function testing 21. Room air desaturation at rest ≤ 85% 22. Females: Pregnant or planning pregnancy 23. Non-cardiopulmonary disorders that may affect exercise performance or be aggravated by exercise (e.g., infection, renal failure, thyrotoxicosis, > moderate GVHD resulting in physical or functional impairment) 24. Parents/guardians or subjects who, in the opinion of the Investigator, may be non-compliant with study schedules or procedures

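### The block sizes are published while exercise assignment is open to the study team, so the next exercise status can be guessed better than chance

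*Protocol article*

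**What the plan says.** Under Participants and randomization, the article allocates four arms within strata of age (18 or over versus under 18) and site, "by a designated study member using REDCAP randomization scheme". It adds: "Balance between arms will be maintained through randomly permuted blocks of size four or eight". NR and placebo are masked from everyone. For exercise the masking is partial: "The outcomes assessor (but not the study team, care providers, or participants) will be blinded". Table 1 (Study type) agrees that exercise assignment "will not be blinded to the participant or majority of the study team".

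The same section has study staff pre-screen charts and invite candidates. Randomisation follows once eligibility has been confirmed in person. One exclusion is a matter of judgement (Table 2, criterion 24): "Parents/guardians or subjects who, in the opinion of the Investigator, may be non-compliant with study schedules or procedures".

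Statistical considerations tests each active arm against control in Stage 1. It compares exercise + NR with exercise alone in Stage 2 only if exercise + NR differs from control. The Trial status section says that recruitment has not commenced. Table 1 gives the status as recruiting, with first enrolment in June 2022.

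**The concern.** Four and eight are the two smallest block sizes that balance four arms. On the exercise factor every block therefore holds two and two, or four and four. Strata are nested in site, so each site's staff can see the whole exercise sequence of their own strata. With the sizes in print, past assignments carry information about the next one. Sealing the REDCap list does not remove this, because the inference uses assignments already made.

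If a guess influenced who was invited, when a baseline visit was booked, or how criterion 24 was applied, the exercise and no-exercise arms could differ in motivation or expected response. The model adjusts for baseline Z-score, which does not measure either. The exposed contrasts are exercise versus control and exercise + NR versus control, and the second decides whether Stage 2 is tested at all.

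**Working it through.** **Inputs from the article.** Block sizes 4 or 8; four strata (two sites by two age groups); 80 randomised; exercise open and NR masked; lower bound of the treatment-related changes 0.93 Z, and 0.73 Z for exercise + NR versus exercise (both from Sample size and power). The article gives no predictability figure to reproduce.

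**Assumptions.** Equal strata, 80/4 = 20 each. Each block is 4 or 8 with equal probability. The guesser knows the sizes and the stratum's exercise history, but not the NR assignments or the size of the current block, and always picks the likelier exercise status.

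**Hand check, size 4 only (two exercise, two not).**
- First place: 1/2 correct.
- Second place: 2/3.
- Third place: certain if the first two match (probability 1/3), otherwise 1/2, so 1/3 + (2/3)(1/2) = 2/3.
- Fourth place: always certain.
- Correct: (1/2 + 2/3 + 2/3 + 1)/4 = 70.8%. Certain: (1/3 + 1)/4 = 33.3%.

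**Simulation.** This applies Bayes' rule exactly to the position in the block, with 20 per stratum and 4,000 replicates.

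| Scheme | Correct | Probability ≥ 0.75 | Certain |
|---|---|---|---|
| 4 and 8, equal mix | about 67% | about 39% | 6–7% |
| 4 only | 71% | – | 33% |
| 8 only | 65% | – | 16% |
| 4, 8 and 12, sizes known | 65% | 30% | 2% |

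For complete blocks of 8, exact enumeration gives 66.6% correct and 20% certain. Twenty per stratum leaves a half block, which explains the lower simulated figures. For the mix of 4 and 8, correct guesses are about 65% with 10 per stratum and 67% with 30. They run from 66% to 69% as the share of size-4 blocks goes from 25% to 75%, and certain guesses from 8% to 4%.

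**Effect of a lag.** If one other participant in the stratum is awaiting randomisation when the guess is made, the figures for the mix fall to about 60% correct, 16% at 0.75 or more, and 3% certain. With two pending they are about 57%, 6% and 1%.

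**Possible bias.** Let d be the difference in expected strength change between people enrolled when exercise is guessed and people enrolled when no exercise is guessed. A share p of the exercise arms, and 1 − p of the no-exercise arms, was enrolled under an exercise guess. The contrast is therefore shifted by d·p − d·(1 − p) = d(2p − 1). With p = 0.674, 2p − 1 = 0.348.
- d = 0.25 Z: 0.25 × 0.348 = 0.087 Z, and 0.087/0.93 = 9%.
- d = 0.5 Z: 0.5 × 0.348 = 0.174 Z, and 0.174/0.93 = 19%.

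The article gives no value for d; this range is an assumption. The direction of any bias is also unknown.

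**Which contrasts.** In exercise + NR versus exercise, both arms exercise, so a guess about exercise cannot separate them. In NR versus control, neither arm does. Masking of NR protects both contrasts.

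**The case against.** The strongest reply is that the opportunity is small. Invitation comes well before randomisation, allocation runs through REDCap after eligibility is confirmed, two block sizes are used, and the model adjusts for baseline Z-score. Few staff would track a sequence as an exact Bayesian guesser does, and one pending participant already removes much of the advantage. Selective enrolment also costs recruits: the Discussion expects 185 potentially eligible people for 80 places and worries about accrual.

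This stands as to size. The 67% is a ceiling, and nothing in the article suggests that staff would steer enrolment. It does not remove the risk. The listed safeguards do not stop inference from past open assignments, the timing of visits and criterion 24 stay at the investigator's discretion, and 185 candidates for 80 places leaves some room to choose. The assessor masked to exercise protects measurement, not selection.

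Several stronger readings are tempting and are not supported:
- **Assignments are often certain.** The 16% to 33% figures need a single fixed size. The article names two sizes, and although it does not say outright that they are mixed at random, a mix gives only 6 to 7%.
- **The bias is about a quarter of the 0.73 Z sizing difference.** That difference belongs to exercise + NR versus exercise, which NR masking protects. The 0.93 Z lower bound is the fairer yardstick.
- **Permuted blocks are an error.** They are a legitimate choice; the weakness is disclosing small sizes for an open factor.
- **The designated study member also recruits.** The article does not say so, and such detail is commonly left to the full protocol.

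**Conclusion.** The point holds as a modest, avoidable risk. The article makes public the two smallest usable block sizes for a factor that the study team sees. A fully informed guesser would then be right for at most about 67% of exercise assignments, with about 39% predictable at 0.75 or more and 6 to 7% certain. These figures rest on 20 per stratum, an equal random mix of sizes and no pending participants; pending participants lower them. Any resulting bias is confined to the exercise versus no-exercise contrasts, including the gate to Stage 2. It would be at most about 0.09 to 0.17 Z for d between 0.25 and 0.5 Z, roughly 9 to 19% of 0.93 Z. A reader might infer that the exercise results will be biased. The article gives no evidence of that, and d is assumed. The change is worth making because it costs almost nothing and analysis cannot reliably repair selection afterwards.

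**What to change.** 1. Regenerate the REDCap allocation list with a wider random mix of block sizes that differs from the published one. Do this before first enrolment, or for the remaining allocations if enrolment has begun. Table 1 and Trial status conflict on which applies, so reconcile them first.
2. Keep the sizes in a document that is not available to anyone who screens, consents or confirms eligibility.
3. Replace the published sentence with: restricted randomisation, details withheld until enrolment closes.

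Withholding the sizes matters as much as widening them. If a mix of 4, 8 and 12 were known, correct guesses would fall only from about 67% to 65%, although certain guesses would fall to about 2% and those at 0.75 or more to about 30%.

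The cost is one new list and one amended sentence, with no extra patients, visits or staff. The downside is slightly looser balance within small strata.

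A biased coin for the exercise factor, with NR then blocked within exercise group, is an option and not a requirement. Take a coin that is fair while the counts in a stratum differ by at most 1, and 2/3 towards the smaller group otherwise. Correct guesses fall to about 57% and none reaches 0.75. The probability that the overall exercise counts differ by 8 or less is 94.8%, so the 95th percentile is about 10 (45 versus 35), against 4 with the mix of 4 and 8. Efficiency on the exercise margin is 4 × 45 × 35/80² = 0.984, a loss of about 1.6%. The cost for the pairwise four-arm contrasts has not been worked out.
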